#### The Dexamethasone Intervention

2.4.1

Patients randomized to Dexamethasone receive 20 mg intravenously (administered as Dexamethasone phosphate) over 15 min as soon as possible after admission, followed by 20 mg intravenously daily at 0600 h (or at least 8 h after the initial dose) for two additional days, for a total of three doses. Patients in the control group receive a matching placebo (sodium chloride).

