#### Early Wakeup Intervention

2.4.4

Patients are randomized to an early wakeup call after ≤ 6 h or a late wakeup call between 28 and 36 h after intensive care unit admission. Criteria for extubation readiness include Glasgow Coma Scale ≥ 12, Richmond Agitation‐Sedation Scale 0 to −1, ability to raise arm or voluntary handshake on command, successful spontaneous breathing trial, and low ventilator settings (pressure support ≤ 14 cm H_2_0 (or lower according to local practice), positive end‐expiratory pressure ≤ 8 cm H_2_O [10 cm H_2_O if obese], and fraction of inspired oxygen ≤ 40%). A wakeup call can be aborted in case of seizures, respiratory distress, shock, or other clinical reasons. Sedatives before the scheduled wake‐up call are permitted as needed for clinical care in the early‐wake‐up call group and are mandatory in the late wake‐up call group.

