### General Principles

3.1

All analyses will be conducted according to the modified intention‐to‐treat principle, including all randomized participants who meet the inclusion criteria and have available outcome data, or imputed outcome data (see missing data section below). Participants who do not fulfill the inclusion criteria will be excluded from analyses. If consent is subsequently withdrawn, data collected prior to withdrawal will be included in the primary analysis in accordance with the EU Clinical Trials Regulations, unless the participant explicitly requests deletion of their data. A per‐protocol analysis will be performed as a sensitivity analysis, including only participants who received all scheduled doses of pharmacologic interventions, adhered to the assigned backrest position for ≥ 80% of the time, and had a wakeup call attempted within the assigned time frames.

Data will be analyzed and reported as four individual trials, with no adjustment for multiple comparisons planned. This approach is justified because almost all previous trials in the hospital phase of out‐of‐hospital cardiac arrest care have been neutral, and all four interventions are accepted without considering potential interactions. If more than one intervention shows a non‐neutral result, interactions between interventions will be evaluated by including pairwise and higher‐order interaction terms in the primary regression models for each intervention, applying the prespecified thresholds defined in Section 3.5 (interaction *p* < 0.01 and absolute effect ≥ 5.6%). If a clinically important interaction is identified, results for the affected interventions will be presented both as overall estimates and stratified by the interacting intervention allocation. All regression analyses will be adjusted for site as a covariate.

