### Limitations

4.2

Several limitations warrant consideration. The analysis plan does not adjust for multiple comparisons across the four interventions, increasing the risk of Type I error. This decision reflects the pragmatic consideration that all four interventions address distinct mechanistic pathways and are justified independently. However, findings will be interpreted cautiously, and interactions will be evaluated if multiple interventions show non‐neutral results. Second, the factorial design assumes no interactions between interventions. While preliminary simulations suggest adequate power even with minor interactions, substantial interactions could reduce power and complicate interpretation. Third, the backrest elevation and early wakeup interventions are unblinded, potentially introducing performance and detection biases. However, primary outcomes (mortality and days alive outside the hospital) are objective and ascertained by blinded assessors. Fourth, the per‐protocol analysis may be affected by selection bias if nonadherence is related to prognosis. Results will be interpreted as exploratory and hypothesis‐generating. Fifth, anticipated intervention effects informing sample size calculations are based on clinical judgment and prior trials, introducing uncertainty. Statistical power may be lower if true effects are smaller.

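### As written, the per-protocol rule makes early survival a condition of entry to a sensitivity analysis of death and days alive, and it leaves open whether one set serves all four interventions

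*SAP article*

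**What the plan says.** Section 3.1 (General Principles) defines the per-protocol set by three criteria joined by 'and': "including only participants who received all scheduled doses of pharmacologic interventions", at least 80% adherence to the backrest position, "and had a wakeup call attempted within the assigned time frames". No clause covers a patient who dies before a dose or call is due. The same section gives the analysis its role ("protocol analysis will be performed as a sensitivity analysis") and says "Data will be analyzed and reported as four individual trials", but not whether there is one per-protocol set or one per intervention.

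The timings are in section 2.4:
- Wakeup (2.4.4): one arm is "randomized to an early wakeup call after ≤ 6 h"; for the other arm the text has "or a late wakeup call between 28 and 36" (hours, counted from admission to intensive care).
- Dexamethasone or placebo (2.4.1): an initial dose, then a daily morning dose "for two additional days, for a total of three doses".
- Olanzapine or placebo (2.4.2): an initial dose and two further evening doses, ending sooner on discharge from intensive care.

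The primary outcomes (2.5.1) are 90-day mortality, and days alive outside hospital within 30 days. Section 4.2 concedes that the per-protocol analysis "may be affected by selection bias if nonadherence is related to prognosis" and treats it as exploratory. Section 4.4 repeats the caution.

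**The concern.** Entry to the set depends on living long enough to receive treatment, while the outcomes are themselves survival outcomes. A late-wakeup patient managed exactly as assigned who dies at 20 h cannot have had a call at 28-36 h, and so fails the criterion. A patient who dies before the third dose cannot have received three doses. Neither departed from the protocol; the definition classes them as if they had.

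Two things are at stake. First, for dexamethasone and backrest, which section 2.5.1 expects may act on early survival, the early deaths may be left out of the check. Second, for wakeup, the survival needed to qualify may differ by arm (up to 6 h against at least 28 h). That would create a difference where none exists, in the direction of the alternative hypothesis printed for wakeup in the Background (more days with mandatory sedation).

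**Working it through.** **The plan's own figures.** Section 2.6 assumes 35% mortality scored as 0 days and 15 days for survivors: 0.65 × 15 = 9.75, stated as 9.8. For a 1.5-day difference, SD 7, two-sided 5% and 90% power, the normal formula gives 458 per arm (916 in total) against the stated 920; 460 per arm gives 90.1% power. These figures are sound, and this point disputes none of them.

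**When the third dose is due.**
- Dexamethasone: taking the second dose as the first 0600 at least 8 h after the initial dose, it falls 8-32 h later. Adding 24 h puts the third at 32-56 h.
- Olanzapine: taking the second dose as the first 6 PM at least 12 h later, it falls at 12-36 h, and the third at 36-60 h.

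Every patient follows both schedules, active or placebo, so on these readings the third doses fall due after 28 h. Dose times run from the first dose and the wakeup window from intensive care admission, so the gap is approximate.

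**What each reading does to a death at 20 h, after an early-arm call made within 6 h.**
1. One joint set, all criteria literal: the patient leaves both wakeup arms through the dose criterion. With no true effect, the between-arm wakeup artefact is about 0, but every comparison is conditioned on early survival.
2. One set per intervention, or doses read as due while alive with calls still literal: the patient leaves the late arm and stays in the early arm.
3. Doses and calls both read as due while alive: the patient stays in both arms, and the artefact is 0.

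**Reading 1, dexamethasone.** The planned effect is 35% × 0.25 = 8.75 points, so 26.25% treated. Assume 10% of controls die before dose 3. Control mortality in the set is (0.35 − 0.10)/0.90 = 27.8%. For treated patients:
- Effect spread evenly (early deaths 7.5%): (0.2625 − 0.075)/0.925 = 20.3%. Difference 7.5 points, RR 0.73.
- Whole effect before dose 3 (early deaths 10 − 8.75 = 1.25%): (0.2625 − 0.0125)/0.9875 = 25.3%. Difference 2.5 points.
- Whole effect after dose 3 (early deaths 10%): (0.2625 − 0.10)/0.90 = 18.1%. Difference 9.7 points, RR 0.65.

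The distortion can therefore go either way. It applies to a dexamethasone-only set as well, since the dose criterion would still be part of it. For backrest, the dose criterion matters only if the set is joint.

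**Reading 2, wakeup, no true effect.** With a share d of an arm removed by early death, mortality is (0.35 − d)/(1 − d) and mean days are 9.75/(1 − d). The documents give no early-death share, so the share e dead by 28 h is assumed. The middle columns remove nobody from the early arm (the upper limit). The last column puts one third of these deaths before the early call, so they leave both arms.

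| e | Late mortality | Early mortality | Gain for late, days | Gain if one third precede the early call |
|---|---|---|---|---|
| 1% | 34.3% | 35.0% | 0.10 | 0.07 |
| 3% | 33.0% | 35.0% | 0.30 | 0.20 |
| 5% | 31.6% | 35.0% | 0.51 | 0.35 |
| 10% | 27.8% | 35.0% | 1.08 | 0.75 |

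The planned effect is 1.5 days.

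**The case against.** The strongest reply is that the one-sided wakeup bias requires reading one sentence two ways. A reader might infer that section 3.1 removes deaths before 28 h from the late arm alone. As printed, the criteria are joined, and the three-dose requirement removes those deaths from the early arm as well. Early-arm patients who die before any call is attempted also leave. This stands: the asymmetry appears only under reading 2. That reading is still open, because the plan reports four individual trials without saying how many per-protocol sets there are, and because 'scheduled' could mean due while alive (the olanzapine schedule already ends at intensive care discharge), whereas a call that was never attempted cannot be read so generously.

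A reader might also infer that the plan declares early deaths non-adherent. It does not; it is silent, and exclusion follows from applying the criteria literally. Nor do the documents support the view that the dexamethasone effect would largely vanish: the 2.5-point figure needs early deaths to fall from 10% to 1.25%, and with an even reduction the relative effect is hardly changed (RR 0.73 against 0.75).

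Finally, sections 4.2 and 4.4 disclose selection bias and limit the analysis to an exploratory role. That contains the harm, but the caveat concerns non-adherence linked to prognosis. Here patients who adhered until death are excluded by the definition, which wording can repair.

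**Conclusion.** The concern holds in limited form. Followed literally, section 3.1 makes survival to the due times a condition of entry to an analysis of mortality and days alive, and the general caveat does not remove this. What it does to the results depends on a choice the plan leaves open:
- With a joint set and three doses required, all comparisons are conditioned on early survival, without a between-arm wakeup artefact under no effect. The dexamethasone contrast moves by an amount and in a direction set by when any benefit occurs.
- With separate sets, or with only doses read as due while alive, late wakeup gains about 0.1-1.1 days from the definition alone, less if some early-arm deaths precede the call.

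These sizes rest on assumed early-death shares (1-10% by 28 h, 10% by dose 3), the plan's 35% mortality, and other exclusions being unrelated to arm. Only an exploratory sensitivity analysis is affected; the primary modified intention-to-treat analysis is not.

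**What to change.** In section 3.1:
- State whether the per-protocol set is joint or defined separately for each intervention and, if separate, which criteria apply to each.
- Define adherence as having received every dose, position check and wakeup call that fell due while the patient was alive and still subject to the intervention. Death before an item is due counts as adherent, with the same wording for both arms of each factor.
- Report by arm how many patients died before each item was due.

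The cost is SAP wording and a few lines of code using times of death, doses and calls. It is best settled before allocation is unblinded. The downside is that a few patients with little exposure stay in the set, which slightly dilutes the contrast.

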### Analysis of Primary Outcomes

3.2

#### Mortality Outcomes (Dexamethasone and Backrest Interventions)

3.2.1

The primary analysis for the Dexamethasone and elevated backrest interventions will use log‐binomial regression to estimate the relative risk of 90‐day mortality, defined as the proportion of patients who die from any cause between randomization and day 90. This will also be reported for the early wake‐up and olanzapine interventions. If log‐binomial models are infeasible due to non‐convergence, logistic regression models will be used instead, and OR will be reported instead of RR. As additional analyses, Kaplan–Meier curves for each allocation group will be estimated, graphically displayed, and compared by the log‐rank test. Furthermore, Cox proportional hazards models will be applied to estimate hazard ratios with 95% confidence intervals for time to death between treatment groups as a secondary outcome for all four interventions. As prespecified subgroup analyses, the interaction between treatment allocation and each of the following baseline variables will be assessed: sex, age, time to ROSC, lactate level upon hospital admission, shockable primary rhythm, witnessed cardiac arrest, bystander‐performed CPR, and presence of STEMI consistent with acute myocardial infarction. Proportional hazards assumptions will be assessed using Schoenfeld residuals and log–log plots. If deviations from the proportional hazards assumption are detected, the relevant covariates will be included with time‐varying HR instead, or if this is not sufficient to solve the deviation, Cox regressions with stratified baseline hazards will be utilized. Further, causes of death (cardiovascular, neurological, multi‐organ failure) between the treatment arms will be compared as competing risks with the Nelson‐Aalen cumulative incidence method as hypothesis generating. Any changes from the pre‐specified analysis plan will be reported.

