### Randomization and Blinding

2.3

Randomization is performed in a 1:1 factorial design for all four interventions, using sealed intervention boxes containing study drugs and written instructions. Randomization is generated with varying block sizes to ensure balance across the 16 possible intervention combinations. The balance of allocation across the 16 possible combinations is monitored when generating the randomization sequence and as part of the planned interim analyses.

Pharmacologic interventions (dexamethasone and olanzapine) are double‐blinded, with study drugs prepared by the pharmacy in the Capital Region of Denmark and administered by nurses uninvolved in the patient's care. Physiologic interventions (backrest elevation and early wakeup) are open‐label because blinding them is inherently difficult. Outcome assessors, statisticians, data managers, the steering group, and the data safety and monitoring committee will be blinded to treatment allocation.

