### Sample Size

2.6

The trial aims to include 1000 patients across five sites, covering the entire Danish population. Sample size calculations were performed separately for each intervention based on its primary outcome.

For the Dexamethasone and backrest elevation interventions (primary outcome: 90‐day mortality), assuming an overall mortality of 35% and a 25% relative risk reduction (to 26% mortality), with 85% power and a two‐sided significance level of 5%, 468 patients per group are required. To account for potential dropouts and loss to follow‐up, 500 patients per group (1000 total) are planned.

For the olanzapine and early wakeup interventions (primary outcome: days alive outside hospital within 30 days), estimates assumed 35% mortality during initial hospitalization (0 days alive outside hospital) and a mean of 15 days outside hospital for survivors, yielding a population mean of 9.8 days with an estimated standard deviation of 7 days. To detect an increase of 1.5 hospital‐free days with > 90% power and a two‐sided significance level of 5%, a total of 920 patients were required.

The combined sample size of 1000 patients provides adequate power for all four primary outcomes within the factorial design. The trial is not powered to detect interactions between interventions; prespecified interaction analyses (Section 3.5) are exploratory and hypothesis‐generating.

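### The primary 90-day mortality model adjusts for site only, so it forgoes power that prespecified prognostic adjustment would give; separately, its non-convergence fallback changes the effect measure from RR to OR

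*SAP article*

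**What the plan says.** - **Model.** SAP section 3.2.1 makes log-binomial regression for the relative risk of death by day 90 the primary analysis for dexamethasone and backrest elevation. It lists no covariates.
- **Covariates.** Section 3.1 supplies the only one: "All regression analyses will be adjusted for site as a covariate".
- **Baseline predictors.** Section 3.2.1 names "sex, age, time to ROSC, lactate level upon hospital admission, shockable primary rhythm, witnessed cardiac arrest, bystander‐performed CPR" and STEMI, but only for treatment-by-subgroup interactions. Section 3.4 repeats the list as subgroups, with age, time to ROSC and lactate split at the median.
- **Other allocations.** The other three interventions are fixed effects in the adjusted models for dichotomous, single-time-point continuous and ordinal secondary outcomes (3.3.1, 3.3.2, 3.3.4), and are adjusted for in the sensitivity model for days alive outside hospital (3.2.2). They are not named for the primary mortality model.
- **Fallback.** If the log-binomial model does not converge, section 3.2.1 says that "logistic regression models will be used instead, and OR will be reported instead of RR". It gives no route back to a relative risk.
- **Sample size.** Section 2.6 takes 35% mortality, a 25% relative reduction (given as 26%), 85% power and two-sided 5%. It concludes that "468 patients per group are required" and that "500 patients per group (1000 total) are planned".

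**The concern.** There are two separate points, with separate causes.

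**Efficiency.** The subgroup analyses need the baseline variables, so the trial must hold them. Variables of this kind are usually related to death after cardiac arrest, and adjusting for predictors of outcome sharpens a randomised comparison. Leaving them out of the primary model gives up precision in a trial whose mortality sample size has almost no reserve at an exact 25% reduction.

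**Effect measure.** The trial is planned on the risk scale, and at about 30% mortality an odds ratio is well away from the relative risk. Under the fallback, the measure reported for a primary outcome would depend on whether an algorithm converged. No mortality risk difference with a confidence interval is named either, although the interaction rule in section 3.5 is set in absolute risk.

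**Working it through.** **Inputs.** From section 2.6: control mortality 35%; intervention 26% as stated, or 0.75 × 35% = 26.25% for an exact 25% reduction; 85% power; two-sided 5%; 468 required and 500 planned per group; five sites. From section 2.3: "Randomization is performed in a 1:1 factorial design for all four interventions". The prognostic strength of the baseline variables is not in the SAP, so it is assumed and varied.

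**1. The plan's own figure.** Two proportions, pooled variance, no continuity correction:

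n = [1.960·√(2·p̄·q̄) + 1.036·√(p₁q₁ + p₂q₂)]² / (p₁ − p₂)²

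- 35% vs 26%: p̄ = 0.305, so n = (1.960·√0.42395 + 1.036·√0.4199)² / 0.09² = 468.4. That is 468 to the nearest whole number and 469 rounded up, so the stated figure reproduces.
- 35% vs 26.25%: the same formula gives 497.
- Power at 35% vs 26%: 85.0% with 468 per group, 87.2% with 500.
- Power at 35% vs 26.25%: 82.8% with 468 per group, 85.2% with 500.

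**2. Effect of adjustment on power.** Simulation with 1000 patients, 500 per arm, five sites and 3000 replicates per scenario. Outcomes were logistic in one standard normal prognostic score, with marginal risks held at 35% and 26.25%. Robust Poisson stood in for the log-binomial RR.

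| Assumed AUC | Site-only logistic | Site-only RR | Adjusted, standardised RR | Adjusted robust Poisson | Gain from standardised RR over site-only RR |
|---|---|---|---|---|---|
| 0.63 | 85.3% | 85.2% | 87.2% | 87.4% | 2.0 points |
| 0.74 | 85.5% | 85.5% | 91.0% | 90.5% | 5.5 points |
| 0.82 | 84.5% | 84.5% | 94.0% | 92.2% | 9.5 points |
| 0.87 | 85.7% | 85.5% | 96.2% | 92.7% | 10.7 points |

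The Monte Carlo standard error near 85% is √(0.85·0.15/3000) = 0.65 points. With no treatment effect, the adjusted analyses rejected in 4.8% to 5.4% of replicates, against a nominal 5% with standard error √(0.05·0.95/3000) = 0.4 points.

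Analytic cross-check at AUC 0.74: a logit-normal risk model with mean 0.31 gives explained variance of about 0.16. The effective size is then 1000/(1 − 0.16) = 1190, or 595 per group. Power is Φ[(0.0875·√595 − 1.960·0.6519)/0.6489] = Φ(1.32) = 91%, which agrees with the simulation.

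**3. The other three allocations.** If each had a 9-point effect, each would explain (0.09/2)² / (0.305·0.695) = 0.002025/0.212 = about 1% of outcome variance, so about 3% together. The gain comes from the prognostic variables.

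**4. Effect of the fallback.**

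- 35% vs 26%: RR = 0.26/0.35 = 0.743; OR = (0.26/0.74)/(0.35/0.65) = 0.653.
- 35% vs 26.25%: RR = 0.750; OR = 0.661.

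A 25–26% reduction in risk would appear as a 34–35% reduction in odds. The two site-only columns show that power is the same on either scale.

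**5. Chance that the fallback is used.** A log-binomial fit fails when fitted risks press against 1. With treatment and five sites as the only terms and control risk 35%, a site would need 1/0.35 = about 2.9 times the average risk to get there. Non-convergence is therefore unlikely in the model as written. It becomes more likely once continuous covariates enter a log-binomial model, so the two points should be settled together.

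**The case against.** The strongest reply is that nothing here is an error. The site-adjusted comparison of randomised groups is valid. Section 2.6 is an unadjusted calculation, and the planned model delivers the power it promises. The gain is measured against a different analysis, rests on AUCs that the SAP does not supply, and is only about 2 points if the predictors are weak. The fallback is prespecified and labelled as an OR, and section 3.1 reports counts with proportions, so a reader can recover the crude RR and risk difference. All of this stands. It limits the weight of the point but does not show the adjusted analysis to be worse: power rose at every AUC tried, and Type I error held.

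A reader might infer three stronger things that the SAP does not support:

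- *The switch to logistic regression loses power.* It does not. Site-only logistic and site-only RR both give about 85%.
- *The trial falls short of its planned power.* It does not: 500 per group give 85.2% at 26.25% and 87.2% at 26%.
- *The dexamethasone and backrest papers are likely to report different measures.* This is possible under the wording but improbable. Both use the same patients, sites and outcome, in a model that should nearly always converge. Convergence is less assured only in fuller models, such as those with the interaction terms of section 3.1.

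**Conclusion.** The point holds as a matter of efficiency and of a consistent effect measure; the randomised comparison is not biased. Adjusting for site alone forgoes about 2, 5.5, 9.5 or 11 percentage points of power at an assumed AUC of 0.63, 0.74, 0.82 or 0.87.

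These figures assume 35% vs 26.25% mortality, one correctly modelled score, complete baseline data, and no mortality differences between sites. The direction is secure, but the size depends on prognostic strength that the SAP does not state.

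The RR-to-OR fallback is a smaller, separate weakness. It would move the reported figure from about 0.74 to 0.65 at the planning rates, at no cost in power, and is unlikely to be triggered by the model as written.

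**What to change.** In section 3.2.1:

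1. Make the primary mortality analysis a logistic regression with treatment, site, the other three allocations and a short prespecified list of baseline predictors. The natural candidates are already named: age, time to ROSC and lactate, kept continuous, with shockable rhythm, witnessed arrest and bystander CPR.
2. Standardise the fitted risks over the trial population and report the marginal RR and the risk difference, each with a 95% confidence interval. Name the RR as the measure that carries the primary test. In Stata this is a logistic fit followed by `margins`.
3. Keep the site-only log-binomial RR as a sensitivity analysis. If it fails to converge, use modified Poisson regression with robust standard errors, not an OR.
4. State how missing baseline values will be handled.

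The cost is SAP wording and code, plus the missing-value rule; the SAP does not say how often baseline values are missing. No new data are needed beyond what the subgroup analyses already require. The change should be dated and made before anyone analyses outcome data by coded allocation.

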### Handling of Missing Data

3.6

Missing data for the primary outcomes are expected to be minimal (< 5%) given the registry‐based follow‐up for mortality and comprehensive hospital records for days alive outside the hospital. The primary analysis will include all participants with available data.

If missing data exceed 5% for primary outcomes and are believed to be missing at random, the following approaches will be used:
Multiple imputation: Missing values will be imputed using chained equations with 50 imputations, incorporating baseline characteristics and treatment allocation to the four interventions, but without including treatment interactions.Best‐worst and worst‐best case scenarios: To assess the potential range of impact of missing data, best‐worst scenarios (all patients with missing data in the intervention group assumed a beneficial outcome; all in the control group assumed a harmful outcome) and worst‐best scenarios (reverse assumptions) will be presented. For numerical outcomes, best, respectively, worst‐case scenarios will be imputed using the minimum, respectively, maximum taken of the numerical outcome over all non‐missing patients.Sensitivity analyses: Additional sensitivity analyses assuming all participants with missing data were either all alive or all dead (for mortality outcomes) will be performed.

For secondary and tertiary outcomes, missing data mechanisms will be evaluated, and multiple imputation will be used if appropriate. Complete case analyses will be reported alongside imputed analyses.

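### Section 3.2.1 names Nelson-Aalen, a cumulative-hazard estimator, for the cumulative incidence of competing causes of death; reported as risks, its values would be too high

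*SAP article*

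**What the plan says.** Section 3.2.1 of the SAP article plans, after the all-cause analyses, that "causes of death (cardiovascular, neurological, multi‐organ failure) between the treatment arms" will be "compared as competing risks with the Nelson‐Aalen cumulative incidence method". The same clause grades the analysis as exploratory: "cumulative incidence method as hypothesis generating".

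No other section names a competing-risks estimator, and this sentence names no test or effect measure for the comparison between arms. The all-cause analyses in the section are specified separately: log-binomial regression for the primary outcome, with Kaplan-Meier curves, the log-rank test and Cox models in addition. Competing causes do not arise there, because the endpoint is "the proportion of patients who die from any cause between randomization and day 90".

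**The concern.** The Nelson-Aalen estimator for one cause adds up deaths from that cause divided by the number at risk. Deaths from other causes simply leave the risk set, as censored patients would. The result is a cumulative hazard, which is not a probability and can exceed 1. The cumulative incidence is the probability of having died from that cause by a given day. With competing causes it is estimated by Aalen-Johansen, which weights each increment by the proportion still alive just before it. The sentence therefore attaches the name of one estimator to the target of another.

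If the name is followed and the output is labelled as incidence, the three cause-of-death curves would each lie too high. Their total would exceed the all-cause mortality shown by the Kaplan-Meier curve in the same report. The excess grows with mortality, so it would also differ between arms whose mortality differs.

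**Working it through.** **Inputs from the SAP article**
- 90-day mortality of 35%, and 26% under the assumed effect (Sample Size).
- Three causes of death, compared to day 90 (Section 3.2.1).
- 500 patients per group planned (Sample Size).
- Missing primary-outcome data expected below 5%, so little censoring before day 90 (Handling of Missing Data).

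**Assumptions, because the document gives no figure for them**
- The three causes cover all deaths.
- The shares of the causes, 60/25/15 as the worked case, and their timing.

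**The plan's own figure.** The document gives no number for the cause-of-death analysis. The one stated figure built on the same mortalities is the sample size: "with 85% power and a two‐sided significance level of 5%, 468 patients per group are required". With 35% against 26%, a mean of 30.5%, and no continuity correction:

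n = [1.960·√(2·0.305·0.695) + 1.036·√(0.35·0.65 + 0.26·0.74)]² / 0.09² ≈ 468.4

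This is 468, or 469 rounded up. The mortality inputs are therefore read as the plan uses them.

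**Formulas.** Let d_k be the deaths from cause k at a time u, Y the number at risk, and S(u−) the proportion alive just before u.
- Nelson-Aalen: H_k = Σ d_k / Y
- Aalen-Johansen: F_k = Σ S(u−)·d_k / Y

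Since S(u−) ≤ 1, H_k is never below F_k, and it is strictly above once any death precedes a death from cause k.

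**Totals over causes.** The hazards add up to H = −ln(1 − M), where M is all-cause mortality, whatever the shares and timing.
- M = 35%: H = −ln(0.65) = 0.431, against incidences summing to 0.350. Factor 0.431/0.350 = 1.23.
- M = 26%: H = −ln(0.74) = 0.301, against 0.260. Factor 0.301/0.260 = 1.16.

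**By cause, with constant shares s over time.** F_k = s·M and H_k = s·H, so each cause carries the same factor as the total. At M = 35%:

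| Assumed share | Aalen-Johansen | Nelson-Aalen | 1 − exp(−H_k) |
|---|---|---|---|
| 60% | 21.0% | 0.258 | 22.8% |
| 25% | 8.75% | 0.108 | 10.2% |
| 15% | 5.25% | 0.065 | 6.3% |
| Sum | 35.0% | 0.431 | 39.2% |

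**Other splits, after conversion.**
- Equal thirds: 3·(1 − 0.65^(1/3)) = 40.1%.
- 90/5/5: (1 − 0.65^0.90) + 2·(1 − 0.65^0.05) = 32.1% + 4.3% = 36.4%.

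**Timing.** With 500 patients, 175 deaths (105, 44 and 26 by cause) and the causes occurring one wholly after another, the factor for a single cause runs from 1.05 (a cause that comes first) to 1.44 (a cause that comes last). In a simulation with overlapping timing (mean times to death of 7, 2 and 6 days for the 60%, 25% and 15% causes), the factors at 35% mortality were 1.27, 1.13 and 1.25.

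**Between arms.** With the same shares in both arms, the ratio of cumulative hazards is 0.431/0.301 = 1.43, and the ratio of risks is 0.35/0.26 = 1.35. The first is a proper comparison of hazards. It is wrong only if read as a ratio of risks.

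**Does a difference in one cause leak into the others?** Keep the 60/25/15 case and halve only the first cause's hazard, so that H = 0.129 + 0.108 + 0.065 = 0.302 and M = 26.0%.
- Nelson-Aalen for the other two causes stays at 0.108 and 0.065.
- Aalen-Johansen moves from 8.75% to (0.108/0.302)·26.0% = 9.3%, and from 5.25% to (0.065/0.302)·26.0% = 5.6%.

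**The case against.** The strongest reply is that the phrase itself speaks of competing risks and of cumulative incidence. It may be a misnamed Aalen-Johansen estimator, in which case the label is wrong and the numbers would be right. Alternatively, the team may mean to show cause-specific cumulative hazards, which is a legitimate competing-risks analysis if the curves are labelled as such. The text does not settle which is meant, so the overstatement is conditional. This part of the reply stands. It does not remove the need for a correction: the article counts independent analysis by two statisticians among its strengths, and one could follow the estimator's name and the other the named quantity and obtain different results.

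It is also fair to say that the analysis is labelled exploratory, that changes from the plan will be reported, and that several between-arm comparisons would be acceptable. All of this limits the weight of the point.

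Two stronger readings are tempting and are not supported. A reader might infer that the plan will certainly report inflated risks; the wording permits unbiased readings. A reader might also infer that under Nelson-Aalen a treatment effect on one cause would spill over into the apparent risk of the others. The reverse is true: the Nelson-Aalen values for the other causes do not move, and it is the cumulative incidences that shift, properly so, because more patients survive to be at risk.

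**Conclusion.** The point holds in conditional form. The named estimator and the named quantity do not match, and nothing else in the article resolves which is meant. If Nelson-Aalen values, raw or converted, are presented as cumulative incidences, every cause with any earlier death is overstated and the causes sum to more than all-cause mortality.

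The raw totals, 0.431 against 0.350 at 35% mortality and 0.301 against 0.260 at 26%, need no assumption about shares or timing, only that the three causes cover all deaths. The figures by cause, and the converted totals of 39.2% (about 36% to 40% for the splits tried), rest on assumed shares held constant over time. They show the order of size and are not bounds. The factor for a single cause also depends on when that cause occurs.

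The consequence is confined to one exploratory comparison. It is worth correcting because the sentence is wrong as written and cheap to put right.

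**What to change.** In Section 3.2.1, replace the phrase with wording such as: *cumulative incidence of each cause of death estimated by the Aalen-Johansen method*. Name the between-arm comparison in the same sentence; Gray's test or cause-specific hazard ratios would each serve, and other choices are acceptable if stated in advance. If Nelson-Aalen curves are also wanted, say that they will be labelled as cause-specific cumulative hazards and not read as risks. Keep the hypothesis-generating label.

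The cost is one sentence of SAP wording. No new data are needed, and the methods are available as standard routines in common statistical software.
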